##### Anthropometric measures

2.7.2.9

Anthropometric measurements will include body mass, height, Body Mass Index (BMI), and circumferences of the waist and neck. Body mass and height will be measured with participants wearing appropriate Physical Education class clothing (shorts and a short-sleeved shirt) and bare feet, using a SECA scale and stadiometer (model 799, Electronic Column Scale, Hamburg, Germany). Body mass will be recorded to the nearest 0.1 kg, and height will be measured in the Frankfort plane to the nearest 0.1 cm. Sitting height, used to estimate biological or somatic age, will also be measured using a stadiometer (Holtain Ltd., Crymmych, Pembs, United Kingdom) equipped with a sit-down drawer. BMI will be calculated as body mass divided by squared height (kg/m^2^) and classified into normal weight, overweight, or obesity categories based on Cole et al.’s cut-off points (76). Waist and neck circumference will be measured using the Executive thin line W606pm tape measure (Lufkin, Mexico). Two consecutive measurements will be taken for each circumference and averaged. All anthropometric measurements will be conducted during baseline and follow-up assessments.

##### Body composition

2.7.2.10

Body composition will be assessed using Dual-energy X-ray Absorptiometry (DXA; Hologic Series Discovery QDR scanner [Bedford, MA], and APEX software, version 4.0.2). DXA is a scanner with high precision for determining body mass (ICC:0.999), lean mass (0.995), fat mass (0.998), and bone mineral content (0.996) (77). The DXA scan will provide data on fat-free mass, fat mass, lean mass index, fat mass index, body fat percentage, visceral adipose tissue, and bone mineral content. In addition, total body less head values will be reported, following the recommendations of the International Society of Clinical Densitometry for pediatric populations (78). Measurements will be conducted individually for each participant during baseline and follow-up assessments.

##### Perceived barriers to ACS

2.7.2.11

Perceived barriers to ACS will be assessed among participants using the BATACE Scale (79). Indeed, the BATACE scale has been considered a validated and reliable tool for evaluating barriers to ACS in Spanish adolescents (*α* ranged from 0.64 to 0.72; and ICC between test and retest ranged from 0.68 to 0.77) (79). The scale includes 18 items that address two key dimensions: environmental/safety factors and planning/psychosocial aspects. The resulting variable for analysis will be the average score across all items, ranging from one to four, where one indicates a low perception of barriers and four indicates a high perception of barriers. Scores will be aggregated by participant and collected during baseline and follow-up assessments. Parental perceived barriers to ACS will be evaluated using the PABACS (Parental Perception of Barriers toward ACS) questionnaire, a validated (rho ranged from 0.20 to 0.31) and reliable tool (ICC ranged between test and retest ranged from 0.51 to 0.55) (80). This questionnaire consists of 23 items divided into three scales: general barriers, walking barriers, and cycling barriers. The final variables for analysis will be the average scores for each scale and individual items, ranging from one (strongly disagree) to four (strongly agree). Data will be aggregated by parent during baseline and follow-up assessments.

##### Autonomy, competence, and relatedness related to ACS

2.7.2.12

Basic psychological needs satisfaction in ACS will be assessed using Basic Psychological Need Satisfaction in ACS Scale (BPNS-ACS) (81). The BPNS-ACS scale have shown a good internal consistency (*α* ranged from 0.81 to 0.92) and a high ICC between test and retest (ICC ranged from 0.76 to 0.81) (81). This scale consists of 12 items that explore participants’ thoughts and feelings about their usual mode of commuting to and from school. Participants will rate their agreement with each item on a five-point Likert scale, ranging from “strongly disagree” to “strongly agree.” The resulting variable will be the average score across all 12 items, aggregated by participant and collected during baseline and follow-up assessments. Motivation for ACS will be evaluated using the Behavioral Regulation in ACS (BR-ACS) questionnaire (82). This scale presents both a high internal consistency (α ranged from 0.70 to 0.91) and ICC (ranged from 0.70 to 0.76) (83). The BR-ACS consists of six factors and 23 items that assess different forms of motivation, including intrinsic motivation, integrated regulation, identified regulation, introjected regulation, external regulation, and amotivation. Participants will indicate their agreement with statements such as “I go or would go to and from school walking or cycling because.” on a five-point Likert-type scale, ranging from “not true for me” to “very true for me.” The final variables for analysis will include average scores for each of the six factors, aggregated by participant and measured during baseline and follow-up assessments.

##### Self-esteem and mental health

2.7.2.13

Self-esteem will be assessed using the validated Spanish version of the Rosenberg Self-Esteem Scale (RSES), consisting of 10 items that evaluate self-respect and self-acceptance (84). This tool has demonstrated satisfactory psychometric properties, with Cronbach’s alphas ranged from 0.83 to 0.86, as well as factorial equivalence was validated using a structural equation model (CFI = 0.912; RMSEA = 0.079), indicating a high degree of invariance (84). In this case, participants will rate their agreement with each item on a four-point Likert scale ranging from one (“strongly disagree”) to four (“strongly agree”). Items 1, 3, 4, 7, and 10 measure positive self-esteem, while items 2, 5, 6, 8, and 9 measure negative self-esteem. The resulting variable will be the average score across all items, with higher scores indicating higher self-esteem. Data will be aggregated by participant and collected during baseline and follow-up assessments. Mental health will be evaluated using the PANASN questionnaire (85), a self-report tool with 20 items which presented a good internal consistency (*α* ranged from 0.75 to 0.76) and an acceptable temporal stability (ICC = 0.84). Ten items assess positive affect (e.g., “I am a cheerful person, I tend to get excited”), and 10 items assess negative affect (e.g., “I feel nervous”). Participants will complete the questionnaire based on how they usually feel and/or behave, using a three-point response scale: “Never” (i), “Sometimes” (ii), and “Often” (iii). The final variables for analysis will be the average scores for positive and negative affect, aggregated by participant and measured during baseline and follow-up assessments.

##### Mode of active commuting to school and related outcomes

2.7.2.14

ACS will be evaluated using the PACO questionnaire^3^, a reliable and valid tool for young Spaniards (Kappa ranged from 0.42 to 0.94) (86, 87). The PACO questionnaire consists of four self-report items designed to assess the usual mode of commuting and the weekly frequency of commuting among children and adolescents. The four questions include: (i) *“How do you usually get to school?”* (ii) *“How do you usually get home from school?”* (iii) *“How did you get to school each day?”* and (iv) *“How did you get home from school each day?”* Participants will select their mode of commuting from predefined options such as walking, cycling, car, motorcycle, bus, public bus, metro/train/tram, or other (requiring mode specification). The main variables of interest are the percentage of usual cycling and active modes of commuting to and from school, along with the weekly number of cycling and active trips. Additionally, participants will report their distance from school and the time it takes to commute from home to school. Response options for distance range from less than 0.5 km to 5 km or more, while response options for travel time range from less than 15 min to 60 min or more (86). Other factors associated with ACS, such as independent mobility, will also be analyzed as secondary variables. Data will be aggregated by participant and collected during baseline and follow-up assessments. Overall, these questionnaires provide valuable data on modes of commuting, frequency of active commuting, distance covered, and time spent during the commute for both adolescents.

##### Cycling skills

2.7.2.15

Cycling skills will be assessed using a specific observational checklist completed by the research staff after each participant’s performance during the *Bikeability* session. The checklist includes 18 cycling skills grouped into six categories: (i) starting off, pedaling, and changing gears; (ii) turning right; (iii) turning left; (iv) performing zigzags; (v) braking; and (vi) unexpected turning. Each skill is scored dichotomously (yes/no), and participants will receive a final score ranging from 0 to 18 points. Data will be aggregated by participant and collected during the *Bikeability* session. The checklist has been previously published, and it is available elsewhere (88).

##### Family socioeconomic status

2.7.2.16

Family socioeconomic status will be assessed using two complementary tools. Adolescents will self-report their family’s socioeconomic status through the Family Affluence Scale III (FAS III; *r* = 0.90 and ICC >0.76) (89). The resulting variables will include composite scores derived from the respective scales, reflecting the level of family affluence. Data will be aggregated by participants and family, and collected during baseline and follow-up assessments.

##### Home-school distance

2.7.2.17

Distance from home to school will be determined using two objective methods. The first method calculates the shortest walking path between the participant’s home and school using Google Maps™ software (52). The second method combines GPS and Geographical Information System (GIS) data to establish the actual route taken by participants between home and school. Additionally, participants and parents will self-report their postal addresses, and the school’s postal address will also be obtained. These addresses will serve as reference points for both methods. The resulting variables will include the calculated shortest distance (km) and the actual route distance (km). Data will be aggregated by participant and collected during baseline and follow-up assessments.

##### Trip characteristics

2.7.2.18

ACS behavior will be objectively evaluated over seven consecutive days using a Q-STARZ BT-Q1000XT GPS device, manufactured by Int Co., Ltd. (Taipei, Taiwan). The GPS will record distance, speed, and trip duration for each commute performed by the participants. Additionally, environmental variables such as terrain slope will be measured and later used as confounders in the analysis. The GPS will be configured with a 15-s epoch to ensure precise data collection. This protocol, which combines GPS data with accelerometry for analyzing ACS behavior, has been previously validated by our research group (17, 20, 31). In this project, the combination will also be used to estimate PAEE associated with different modes of commuting to school. The main variables of interest include distance (km), average speed (km/h), and trip duration (minutes). Data will be aggregated by participant and collected during baseline and follow-up assessments.

##### Weather

2.7.2.19

Ambient and weather conditions will be assessed using two complementary methods. In Phase I, ambient temperature will be measured using iButtons (S-1922 L, Thermochron; resolution: 0.0625°C; Maxim, Dallas, USA). Participants will wear an iButton attached to their trousers to measure outdoor temperature. It is important to note that the iButton device has also demonstrated a very high correlation with a mercury thermometer (r > 0.999) for measuring ambient temperature (REF). Data from the iButtons will be analyzed using the Temperatus software (see Footnote 2) (90). In Phase II, temperature (maximum, minimum, and average), total rainfall, and average wind speed will be obtained from the National Weather Data Bank. This open-source database contains climatological information recorded by observatories across the country. Data will be collected from the weather station closest to each school for the five weekdays and the preceding weekend prior to completing the student questionnaire. These variables will be recorded at both baseline and follow-up. The main variables of interest include daily ambient temperature (°C), total rainfall (mm), and average wind speed (km/h). Data will be aggregated by participant and city.

##### School characteristics

2.7.2.20

School characteristics will be assessed using various measures. School size will be determined based on student enrollment, reflecting the total number of students enrolled during the study period. School socioeconomic status (SES) will be established using data from previous studies (91). Additionally, the socioeconomic status of the school neighborhoods will be objectively analyzed and classified as high or low using GIS. Moreover, the length of the cycling lane network within a 5.1 km street-network buffer around each school will be calculated using GIS (92). Additionally, school staff will be asked to provide information on the availability of bicycle racks either on school premises or near the main entrance. School engagement, which may influence the effects of the intervention, will be assessed through the perceptions of the research staff. Engagement will be categorized into three dimensions: teacher engagement (average staff perceptions of teacher involvement across all classes), student engagement (average staff perceptions of student participation across all classes), and overall school engagement (average of teacher and student engagement scores). Data for all variables will be collected during baseline and follow-up assessments and aggregated by participant and school.

### School-based cycling intervention program

2.8

The school cycling intervention program will include 1 week of training and familiarization with the bicycle using the *Bikeability* methodology (88), and the adolescents’ commuting to and from the school for 8 weeks with the support of encouragement strategies during the intervention. *Bikeability* sessions will have the objective of familiarizing the students with cycling to and from school. This is based on the fact that participants will know how to cycle, but many of them might not have cycled for a long time and have not cycled regularly. Moreover, *Bikeability* sessions will help the research staff to analyze if any student does not have sufficient capacity to carry out the intervention. The *Bikeability* methodology, previously tested and published as innovative material by our research group (88), will consist of two sessions over a one-week period delivered by the research group with the support of the Physical Education teacher during Physical Education class to acquire practical skills and understand how to cycle safely and effectively. The components and content of these two sessions focus on: (i) knowledge about road safety regulations, safety equipment for cyclists, hand signals while cycling, and the benefits of cycling as a means of transportation, and (ii) cycling-related skills. Prior to the first session, the Physical Education teacher will provide students with educational theoretical material to raise awareness about the benefits and usefulness of cycling as a mode of travel, knowledge about road safety rules for cyclists, knowledge about safety equipment for cyclists for both the cyclist and the bicycle, and hand signals while cycling in an urban context. The sessions conducted by the research group with the support of the Physical Education teacher are described below:

Closed Circuit Session (60 min—first day): A practical session will be conducted at the school facilities to learn or improve the fundamental cycling skills necessary for safe biking. Participants will practice how to properly use a helmet and inspect the bicycle before riding, as well as fundamental cycling skills through 10 activities and a cycling circuit. The content will include proper helmet fitting, bicycle safety check before riding, fundamental cycling skills for starting and pedaling, braking safely, shifting gears, and hand signals for changing direction.Closed Circuit Session (60 min—second day): During the second session, the knowledge about the use and maintenance of bicycles will be reviewed, in addition to the cycling skills practiced in session one for their corresponding evaluation. It is important to note that the cycle skills results will be highly dependent on participants’ prior cycling skills, but this session will help to reinforce the skills of those who do not cycle regularly.

The participating schools will provide the necessary materials for the *Bikeability* sessions, such as signaling objects (cones and hoops) to build the circuits. Regarding the methodology, the sessions will encourage student participation, and the language used for communication will be inclusive and adapted to them. Active participation of the students will be promoted through questions, fostering dialog, and providing meaningful individual and group feedback. Additionally, based on previous interventions (45), some alternative strategies will be considered for implementing the *Bikeability* methodology: (i) half of the students will perform the activities first, followed by the other half; (ii) students from one class can lend their bicycles to students from another class; (iii) some secondary schools have their own bicycles that are offered free of charge to students; and (iv) local transport organizations or transportation can be asked to lend bicycles for the intervention. Detailed visual information on the *Bikeability* sessions can be found at the following link.^4^

The second part of the intervention will consist of an eight-week program cycling to and from school. The duration of 8 weeks for school cycling is appropriate in this setting according to a previous systematic review (47). During the eight-week intervention, adolescents will receive an encouragement strategy every week in the form of a challenge related to knowledge content about the importance of PA and having good physical condition for our health, benefits of ACS, knowledge of RMR, PAEE, and its importance, promotion of confidence and motivation for adolescents to travel safely in their environment. The functioning of these encouragement strategies, called Octopus Strategy, will consist of eight games that will be opened weekly as the intervention progresses. In each of the games a series of points will be obtained, and these will be accumulated so that there will be a competition between the different participating schools. The winner of the Octopus strategy will be the participant who completes all the games during the 8 weeks. It is important to highlight that although motivational strategies will be employed to support adherence to the intervention, they are not intended to address broader behavior change processes, such as altering participants’ attitudes or intentions toward active commuting. Thus, the Octopus strategy will aim to improve the adherence and motivation to the intervention (i.e., to cycle at least 3 days to and from the school). Table 4 shows a summary of the project’s objectives related to the *Bikeability* sessions and the contents to be developed in the encouragement strategies, during the eight-week intervention. More information about the different challenges proposed by our research group as an encouragement strategy in the Supplementary material and in the following link.^5^

**Table 4 tab4:** Eight-week school-based cycling intervention overview: octopus strategy.

Activity		Aim	Content	Instrument (target)
1 (week 1 and 2)	Training 1:Bikeability	2, 4 & 5	Implementation of the basic guidelines for bicycle maintenance, in addition to the rules for entry, exit and parking of the bicycle Knowledge and practice of cycling skills on a circuit closed to traffic Practice driving skills on closed circuits to traffic	Bicycles, helmets, first aid kits, cones, and whistle. Student skills evaluation sheet (adolescents/teachers)
2 (week 2)	Encouragement strategies	2	Importance and knowledge of energy expenditure	Infographics (adolescents/teachers)
3 (week 3)	Encouragement strategies	2	Knowledge of World Health Organization recommendations on daily physical activity, as well as its benefits Importance of good physical condition for health	Infographics (parents/adolescents/school center/teachers)
4 (week 4)	Encouragement strategies	1 & 2	Contribution of active commuting to/from school on daily physical activity, as well as its benefits	Infographics (parents/adolescents/school center/teachers)
5 (week 5 and 6)	Encouragement strategies	3, 4 & 5	Positive messages and advice on safe routes for cycling (determining factors of intention or attitude)	Motivational videos (parents/adolescents/school center/teachers)
6 (week 7)	Encouragement strategies	4 & 5	Traveling with family and friends in a fun and safe way	Motivational videos (parents/adolescents)
7 (week 8)	Encouragement strategies	3, 4 & 5	Confidence and motivation to cycling (behavioral control)	Motivational videos (parents/adolescents/school center/teachers)

### Adverse events

2.9

Cycling is generally recognized as a safe and well-tolerated form of PA for adolescents. However, any potential adverse events will be carefully monitored throughout the intervention period. Minor adverse events not directly related to the intervention (e.g., seasonal allergies, weather) and those commonly associated with PA (e.g., fatigue) will not be systematically recorded unless they lead to a modification of the intervention protocol (e.g., the participant is unable to cycle to and from school at least 3 days/week). In such cases, the principal investigator will review the situation and decide whether the participant can continue in the study. On the other hand, in the event of any significant health-related issues, such as a serious injury, these incidents will be assessed by the research team. Again, the principal investigator will review the case and make informed decisions regarding participant safety, including whether the participant can remain in the study. If the participant manages to recover in time and is able to cycle to and from school 3 days/week, he/she will not be allowed to return to the intervention without providing medical clearance to support their resumption of PA. The safety and well-being of participants remain the primary focus of the research team. All adverse events will be systematically monitored, recorded, and reported in future manuscripts to ensure transparency and accountability. To achieve this, the research team will maintain a dedicated document to capture details such as the type, duration, and resolution of adverse events.

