
**Table 1 tab1:** Schools’ inclusion and exclusion criteria.

Inclusion criteria	Exclusion criteria
The school has a specific space for parking bicycles and allows their parking	The school does not have specific infrastructure to park or store bicycles
The school has at least two classes per grade	The school offers bus transportation to the adolescents
At least eight students from the school will agree to participate in the study	The school is already participating in other interventions focused on promoting healthy behaviors
Schools from urban areas	The school has implemented an intervention to encourage commuting to school within the last year
	Schools from rural areas

**Table 2 tab2:** Participants’ inclusion and exclusion criteria.

Inclusion criteria	Exclusion criteria
Adolescents’ females and males aged from 12 to 17 years old (both ages included)	Adolescents younger than 12 years or older than 17 years
Healthy participants who can ride a bicycle safely and without difficulty.	Participants with any injury or medical condition that prevents safe participation in cycling to and from school
Be able to cycle to and from school at least 3 days per week during eight consecutive weeks (Intervention group)	Insufficient ability to ride a bicycle or inability to cycle to and from school at least 3 days a week (Intervention group)
Not to cycle to and from school more than 3 days a week during the last year	Participants who have cycled to and from school more than 3 days a week during the past year
To present a valid signed consent from their parents or legal guardians	Participants without a valid, signed parental or guardian consent form
To present valid data at baseline and follow-up from all the outcomes assessed	Participants who do not provide valid data for all assessed outcomes at baseline and follow-up

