### Description and rationale of the ENERGYCO study

2.5

In Phase I the PAEE of different modes of commuting will be quantified by analyzing each participant individually in different controlled environments. For phase II, after recruiting schools and participants, an eight-week school-based cycling intervention will be implemented. The choice of an eight-week duration was based on the results reported in the systematic review by Dorothea et al. (47) on the effects of cycling interventions in a school setting. For example, although interventions lasting longer than 8 weeks demonstrate positive changes in physical fitness (43, 48), they also exhibit lower adherence, with a higher dropout rate among participants post-intervention. Therefore, considering that interventions lasting 4 to 8 weeks show effects on self-efficacy (49) or PA levels (50) and report a lower dropout rate, an eight-week duration was chosen for the school-based cycling intervention. The intervention will consist of adolescents having to cycle to and school for eight consecutive weeks. To encourage participants to complete the intervention, they will take part in a *Bikeability* training and different encouragement strategies will also be used during this period. Moreover, the ENERGYCO school-based cycling intervention shows relevant factors described in the current National Education Law for the curriculum of Compulsory Secondary Education. This approach is based on strategies proposed by the Active Living by Design Community Action Model (51), which involves preparing through the development of interventions, promoting education, and motivating students to cycle anywhere, as well as organizing activities with incentives and programs to engage participants. Regarding the control groups, participants in these schools will be asked to continue their daily habits. In addition, at the end of the eight-week cycling intervention in schools, control schools will be given the opportunity to conduct the *Bikeability* sessions and will receive all the motivational strategies used for the participating adolescents.

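### Section 2.9 gives two incompatible recording rules for certain minor adverse events, and the restrictive rule can in practice be triggered only in the cycling arm

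*Protocol article*

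**What the plan says.** Section 2.9 (Adverse events) of the protocol article contains both statements.

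- **Restrictive rule.** It covers minor events without a direct link to the intervention (the examples are seasonal allergies and weather) and ordinary effects of activity (the example is fatigue). These "will not be systematically recorded unless they lead to a modification of the intervention protocol". The example of such a modification is that "the participant is unable to cycle to and from school at least 3 days/week".
- **Comprehensive rule.** At the end of the section: "All adverse events will be systematically monitored, recorded, and reported in future manuscripts to ensure transparency and accountability". To this end, "the research team will maintain a dedicated document to capture details such as the type, duration, and resolution of adverse events". No limit by severity or by arm is attached to that document.

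Significant events are handled separately: "in the event of any significant health-related issues, such as a serious injury, these incidents will be assessed by the research team", with no reference to the trigger or to the arm.

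Two other places define what each arm does. Table 2 (section 2.4.1) lists as an inclusion criterion "Be able to cycle to and from school at least 3 days per week during eight consecutive weeks (Intervention group"; its bracketed label confines the requirement to that arm. Section 2.5 says: "Regarding the control groups, participants in these schools will be asked to continue their daily habits". Control schools are offered the Bikeability sessions only once the eight weeks are over.

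Section 2.11 mentions adverse event control sheets among the stored project files. Section 2.10.2 describes no safety analysis, and Table 3 lists no safety outcome.

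**The concern.** Systematic recording of the same events is denied in one sentence and promised in another. Study staff cannot follow both. If they follow the restrictive rule, a later paper that claims to report all adverse events will be inaccurate, because some were never written down.

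The restrictive rule also treats the arms unequally. Whether an exempted event enters the log depends on whether it changed the intervention, and only one arm receives the intervention during the eight weeks. A reader who sees these events listed by arm would be comparing two different recording practices. Participants are aged 12 to 17 and are being asked to cycle to school, and the section itself makes their safety the main priority, so the safety report should mean what it says. Events that were not logged at the time cannot be recovered reliably afterwards.

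**Working it through.** The article gives no adverse-event figure to reproduce. The check is a comparison of texts, followed by a short illustration.

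**Step 1: do the two rules conflict?**

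| Class of event | Restrictive rule | Comprehensive rule |
|---|---|---|
| Minor, no direct link to the intervention, cycling unaffected | Not systematically recorded | Recorded and reported |
| Ordinary effect of activity (e.g. fatigue), cycling unaffected | Not systematically recorded | Recorded and reported |
| Either of the above, leading to a change in the intervention | Recorded | Recorded and reported |
| Minor, directly due to cycling, not an ordinary activity effect | Outside the exemption | Recorded and reported |
| Significant, such as a serious injury | Outside the exemption | Recorded and reported |

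The conflict is confined to the first two rows.

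**Step 2: who can meet the trigger?** The trigger is a modification of the intervention protocol. The one example is inability to meet the 3-days-a-week cycling requirement. Table 2 attaches that requirement to the intervention group, and section 2.5 has controls carry on as usual. A control participant has no intervention to modify during the eight weeks. The example is introduced as only one possibility, but any other modification of the intervention would face the same obstacle. That the trigger is specific to one arm is therefore an inference, and it follows from the arm definitions.

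**Step 3: what would the log show under the restrictive rule?**

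Inputs:
- *n*, participants per arm: 50 per arm in each of 3 cities (section 2.4.2), so 3 × 50 = 150.
- *r*, true share with an exempted-class event, taken as equal in both arms: 20%. Assumption, not in the documents.
- *s*, share of those events that limit cycling enough to trigger recording: 10% to 30% in the cycling arm. Assumption, not in the documents.
- *s* in the control arm: 0, from step 2.

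Formulas: true events = *n* × *r*; recorded events = *n* × *r* × *s*.

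- True events, each arm: 150 × 0.20 = 30.
- Recorded, cycling arm: 30 × 0.10 = 3, up to 30 × 0.30 = 9.
- Recorded, control arm: 30 × 0 = 0.

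The totals change with *r* and *s*, but two features do not. The control count is zero whatever the true rate, and the cycling arm's count falls short of the truth whenever *s* is below 1. An apparent excess in the cycling arm would appear even though the arms were assumed identical.

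**The case against.** The best reply is that the section can be read coherently: the earlier sentence sets a recording threshold, and *all* at the end means all events that pass it. The defect would then be loose drafting in a condensed article, with the detail held in the adverse event control sheets that section 2.11 mentions. That reading is possible, but the text does not state it, and the dedicated document is described without any threshold. Even if it were adopted, the threshold would remain one that only the cycling arm can cross.

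A second reply is proportionality: logging every instance of tiredness in a school cycling programme may not be worth the effort. That is a fair design choice. It justifies leaving a class out in both arms and saying so. It does not justify a rule that admits the class in one arm only, or a promise to report everything.

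Three stronger readings are tempting, and the documents do not support them.

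- *A reader might infer that minor events in general go unrecorded, or that the cycling arm logs only events that change the intervention.* The exemption is narrower. Minor events directly due to cycling that are not ordinary activity effects are outside it, and significant events are assessed whatever their effect on cycling.
- *A reader might infer that the rule discards the harms this intervention is most likely to cause.* The only activity-related example given is fatigue. Nothing suggests that injuries or traffic incidents are dropped.
- *A reader might infer that a planned safety comparison is invalid.* None is planned. What is affected is the comparison a reader would make from the published counts.

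**Conclusion.** The point holds in a limited form. Section 2.9 contradicts itself on whether two classes of minor event are systematically recorded. Under the restrictive rule, the recorded counts for those classes would differ by arm through the rule alone, and a report of *all* adverse events would be inaccurate.

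The actual size cannot be determined from the documents. The 3 to 9 against 0 shown above rests on an assumed 20% event rate and an assumed 10% to 30% triggering share, and on the restrictive rule prevailing in practice, which the text leaves open. If the closing sentence prevails, the imbalance disappears.

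Recording of significant events and of minor events directly due to cycling that are not ordinary activity effects is unaffected, as are the primary outcomes and every planned test. This is a correction worth making before Phase II data collection, so that the promised safety report is accurate.

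**What to change.** Replace the two statements in section 2.9 with one recording rule that:

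- does not depend on whether the intervention was modified;
- applies in the same way to both arms over the same period;
- uses the adverse-event document and control sheets already planned, adding fields for arm, relatedness to the intervention and effect on cycling;
- leads to counts reported by arm.

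If the investigators prefer to leave some class of minor event unrecorded, they should define it without reference to cycling, exclude it in both arms, and replace the promise to report all adverse events with a statement of the class actually recorded.

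The cost is a change of wording and a few more entries in a log that will exist anyway. No new weekly questionnaire for controls is needed; that would add a contact in an arm asked to keep its habits. The follow-up assessment, which both arms attend, is an existing occasion on which both could be asked the same question. The rule should be settled before Phase II starts.
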